## **Statistical Methods**

### ***Quantitative data analyses***

All tests will be based on a nominal 5% two-sided type I error probability. Confidence intervals will have nominal 95% coverage. All primary analyses will compare arms by measures of feasibility.

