Aim 2: Develop a narrative-based stigma reduction intervention and tailor it to the rural primary care setting using HCP feedback.

Aim 3: Assess the feasibility and acceptability of a stigma-reduction intervention in a pilot study in a diverse group of rural primary care HCPs.

To adapt existing interventions, we will disseminate a focused survey to 300 rural primary care physicians in Ohio, assessing key features of stigma and the relationship to buprenorphine attitudes and use. Prior to screening, we will also pre-test all survey items with 25 health care professionals with similar characteristics to our target population. The pilot will assess survey length, and check response distribution, item comprehension, and data collection procedures.

To assess intervention components, we will provide the intervention to 15 rural health care professionals and conduct a structured focus group to explore each module, assess perceptions of the intervention, identify the most salient features, and isolate barriers of concern to inform the development of a booster module.

To understand perceptions of each component in greater depth, we will conduct in-depth interviews with 15 rural health care professionals who have received the intervention.

Following completion of the booster module, we will provide the intervention to 15 rural additional health care professionals and conduct a structured focus group to assess perceptions of the booster module, identify needed changes to each module in the overall intervention, and finalize the intervention for feasibility testing.

Screening, enrollment, randomization and assessments. We will enroll 400 HCPs across 6 rural FQHCs who (1) currently practice in Ohio and (2) are eligible buprenorphine prescribers under federal law (3) do not currently prescribe buprenorphine at full capacity. Primary care providers will include physicians with board certification in internal or family medicine as well as family nurse practitioners. Because our primary outcomes are intervention feasibility, clinics will be cluster randomized into a group of 4 (intervention arm, n=267) and 2 (control arm, n=133) to increase the amount of pilot data on the intervention. We will recruit practices from Federally Qualified Health Centers (FQHCs) and FQHC look-alikes in rural, Ohio counties affiliated with OACHC. All eligible participants in enrolled practices will be screened for eligibility and asked to complete the study.

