#### **Expected effect size and power:**

Given that this is a pilot study that will be used to power a future R01, we do not have sufficient data about the psychometric properties of the outcome measures utilized in this study among our population of interest, including the means and standard deviations. As such, we cannot estimate the specific degree of change we can detect in terms of scale points. Thus, the sample size estimation is based on a differences-in-differences cluster randomized trial with two parallel arms and a continuous outcome variable. Alpha was set to 0.05 and power was estimated at 80%. We estimate retention to be 90% at 6 months, due to limited job turnover within community health centers enrolled in the study. Based on these assumptions, a sample of 400 provides 80% power to detect a difference of  $d = 1.01$  with participants clustered in 6 clinics. This indicates we will have sufficient power to assess a difference of one standard deviation in each of the primary outcome variables.

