#### **Analyses of primary outcomes:**

Buprenorphine prescribing outcomes.

We will apply a generalized linear mixed model (GLMM). The GLMM will include subject ID as a random effect and clinic as a fixed effect; the appropriate link function will be used, invoking generalized estimating equations (GEE) to account for the longitudinal (repeated measures) aspect of the data. Using GEE accounts for the repeated-measures design and uses all available data, including participants who may have missed time points and accounts for the correlation between repeated outcome measures at two time points (at 3 and 6 months). We will specify a Gaussian error distribution and identity link to compare the means of each feasibility outcome between the two arms. The primary model will estimate effects across all time points; a secondary model will include an interaction term with time to estimate effects at 3 and 6 months separately.

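### With six clinics randomised 4:2 and no clinic-level degrees of freedom or small-sample correction, the planned GEE approach does not deliver the stated 5% tests and 95% intervals for the arm comparison

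*Combined protocol and SAP*

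**What the plan says.** - **Error rates.** The Quantitative data analyses section sets, for every analysis, "All tests will be based on a nominal 5% two-sided type I error probability. Confidence intervals will have nominal 95% coverage". It adds that the primary analyses compare the arms.
- **Design.** Section 4.1.a says "We will enroll 400 HCPs across 6 rural FQHCs" and that "clinics will be cluster randomized into a group of 4 (intervention arm, n=267) and 2 (control arm, n=133"). Clinics, not participants, are randomised.
- **Model.** Analyses of primary outcomes specifies a generalized linear mixed model with participant as a random effect and clinic as a fixed effect, "invoking generalized estimating equations (GEE) to account for the longitudinal (repeated measures) aspect of the data". The correlation it addresses is between the 3- and 6-month measurements on the same participant. The secondary outcomes follow the same approach.
- **Planning.** The section on expected effect size and power says "Alpha was set to 0.05 and power was estimated at 80"%, and "We estimate retention to be 90% at 6 months". It gives a detectable difference of d = 1.01 with participants clustered in six clinics, but no intracluster correlation (ICC).

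The documents name no reference distribution, degrees of freedom, small-sample standard-error correction or clinic-level clustering unit for the arm comparison.

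**The concern.** GEE standard errors and normal-based tests are justified when there are many independent units. Here the independent units for the arm contrast are the six clinics, which leaves 6 − 2 = 4 degrees of freedom, and one arm has only two clinics. Between-clinic variation estimated from so few units is very uncertain. The usual robust standard error is also biased downwards in this setting.

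If the stated error rate and coverage are not met, differences in prescribing and on the secondary scales will be called significant too often when there is no effect, and the intervals will be too narrow. The outcome table says the adoption measure is to supply preliminary effect sizes for a follow-up cluster randomised trial, and the power section says the pilot will be used to power a later grant. Overstated precision would therefore carry into the next design.

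**Working it through.** **Inputs from the documents.** Six clinics split 4:2; 400 participants, so 400/6 = 66.7 per clinic; 90% retention, so 360 analysed and 360/6 = 60 per clinic; two-sided 5%, critical value 1.96.

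**Assumed, because the documents give no figure.** The ICC; equal clinic sizes unless stated; normally distributed clinic means; one value per participant.

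**The plan's own figure.** With detectable d = (1.96 + 0.84) × √[(1/4 + 1/2)(ICC + (1 − ICC)/m)], d = 1.01 is returned only at an ICC of about 0.16. With a t reference on 4 df it is returned at about 0.08. Without clustering, d would be 0.30 (N = 400) or 0.31 (N = 360). The stated 1.01 can be neither confirmed nor refuted, and it does not show which reference distribution was used.

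**Reading 1: as written, clinic fixed.** Arm is constant within clinic, so its column is a sum of clinic indicators. Six clinic columns plus arm make 7 columns of rank 6. The arm main effect over 3 and 6 months is not estimable, so this reading has no error rate.

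**Reading 2: drop clinic, cluster on participant.** The true variance exceeds the assumed one by 1 + (m − 1) × ICC, and size = 2 × [1 − Φ(1.96/√(1 + (m − 1) × ICC))]. With m = 60:
- ICC 0.01: factor 1.59, size 0.12
- ICC 0.05: factor 3.95, size 0.32
- ICC 0.10: factor 6.90, size 0.46

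**Reading 3: cluster on clinic, uncorrected robust standard error.** With equal clinics the variance estimate is SS_int/16 + SS_ctl/4, where SS is the within-arm sum of squares of clinic means. Its expectation is 3/16 + 1/4 = 0.4375 σ², against a true (1/4 + 1/2) σ² = 0.75 σ², with σ² the variance of a clinic mean.

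**Reading 4: correct model-based (pooled) clinic-level standard error with a normal reference.** Size = P(|t₄| > 1.96) = 0.1216, coverage 87.8%.

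Null simulation on clinic means, 4 v 2:

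| Standard error | Reference | Type I error | Coverage |
|---|---|---|---|
| Uncorrected robust | z | 0.230 | 0.770 |
| Uncorrected robust | t, 4 df | 0.119 | 0.881 |
| Pooled between-clinic | z | 0.121 | 0.879 |
| Pooled between-clinic | t, 4 df | 0.050 | 0.950 |
| Mancl-DeRouen | z | 0.097 | 0.903 |
| Mancl-DeRouen | t, 4 df | 0.041 | 0.959 |

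**Checks on the 23%.** It does not depend on the ICC when clinics are equal (0.229 to 0.231 for ICC 0.001 to 0.20). Fitted exchangeable GEEs on participant-level data gave 0.229 (ICC 0.05, 3,000 replicates). For an assumed unequal set of sizes (20, 40, 80, 100 v 30, 90) it was 0.23 to 0.26 with exchangeable weights and 0.27 to 0.32 with independence weights.

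**Width of the corrected intervals.**
- Same correct standard error: 2.776/1.96 = 1.416.
- Pooled variance with t on 4 df, against the uncorrected robust z interval: √(0.75/0.4375) × 1.416 = 1.85.
- Mancl-DeRouen with t on 4 df, against the same interval: expected variance 3/9 + 1 = 1.333 σ², and √(1.333/0.4375) × 1.416 ≈ 2.5.

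The last two ratios use expected variances, so they are approximate.

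**The case against.** **The 23% is not this plan's error rate.** A reader might infer that the trial as planned would reject a true null 23% of the time. The documents do not support that. The 23% belongs to a GEE clustered on clinic, with an uncorrected robust standard error and a normal reference. The plan's GEE is there for repeated measures on a participant, and the plan states no reference distribution. This objection stands, and the figure must be labelled conditional. It does not rescue the plan, because the literal model has no estimable arm effect and the large-sample repairs above miss 5%. Clustering on participant alone would hold 5% only if the ICC were zero.

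**The clinic term is the more basic defect.** That is true, and degrees of freedom cannot be settled until it is rewritten. But correcting only that term leads naturally to Readings 2 to 4, so the small-sample statement has to be made at the same time.

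**The levels are called nominal, and this is a pilot.** Nominal names the intended level. A true level more than twice that is beyond ordinary approximation error. The pilot purpose is a good reason to play down p-values, but not to report intervals that are too narrow for planning the next trial.

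**Randomisation test.** A reader might also infer that no valid 5% test exists, because a 4:2 split has C(6,2) = 15 allocations and a randomisation p-value cannot fall below 1/15 = 0.067. The count is right, but the plan proposes no randomisation test, so it shows no error. A t test on 4 df does reach 5% if clinic means are roughly normal.

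**Conclusion.** The concern holds in conditional form. The plan states 5% tests and 95% intervals for a contrast with 4 clinic-level degrees of freedom, and specifies nothing that would deliver them. The literal model cannot estimate the arm main effect. Under the repairs examined, the true level is about 12% (model-based clinic-level standard error with z), about 23% (clinic-clustered robust standard error with z, roughly equal clinics), or a level that rises with the ICC when clustering is on participant only. That last level passes 23% at an ICC of roughly 0.03.

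The 12% and 23% do not need an ICC when clinics are equal, but they assume approximately normal clinic means. The participant-only figures rest on assumed ICCs. The planning figure of d = 1.01 does not settle which reference was intended. A sound level is attainable with these six clinics, so this is a correctable gap in the analysis plan and does not invalidate the trial.

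**What to change.** Make this change together with the correction of the clinic term, in both Quantitative data analyses and Analyses of primary outcomes. State that all between-arm p-values and 95% intervals, for primary and secondary outcomes, come from clinic-level inference with a t reference on 4 df (six clinics minus two arms). Name one method in advance:

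- a two-stage analysis of clinic means with pooled between-clinic variance (size 5% under normality);
- a mixed model with clinic as a random effect and between-within degrees of freedom of 4; or
- GEE clustered on clinic with Mancl-DeRouen standard errors and t on 4 df (size about 4%).

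If Kenward-Roger is preferred, say that its degrees of freedom are estimated and may differ from 4. State that the interval is the main reported result and that between-arm p-values are exploratory. The 15-allocation limit may be noted as context.

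**Cost.** SAP wording and a software option, with no extra participants or data. Intervals are about 42% wider than normal-based ones with the same correct standard error. Against the uncorrected robust z interval they are roughly 85% wider (pooled variance, t on 4 df) to about 2.5 times as wide (Mancl-DeRouen, t on 4 df).

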## Section 4: Protocol Synopsis

### 4.1 Study Design

#### 4.1.a. Detailed description

Rural counties, particularly in Appalachia, are battling fast-growing outbreaks of HIV. One of the most promising mechanisms for reducing HIV transmission in these communities is the use of buprenorphine which treats opioid use disorder and also decreases HIV risk. Despite the potential benefit of buprenorphine, health care professionals (HCPs) in rural areas of the United States are much less likely to have received the training and federal waiver necessary to prescribe this medication. The single biggest obstacle to extensive MOUD use is stigma—stigma among communities, families of people who use drugs (PWUD), and remarkably, among HCPs.

We recently completed a study demonstrating that OUD-related stigma is common among physicians in Ohio. This stigma is greater among physicians practicing in rural areas—the same areas experiencing the greatest impact of the opioid crisis. Stigma is also associated with fewer buprenorphine prescribers, syringe service programs, and naloxone dispensaries in the surrounding county. Physicians' stigma toward PWUD is predicted by 3 key attitudes that are unique to the opioid crisis and which require tailoring of existing training interventions.

Rural health care professionals would benefit from brief stigma-reduction training interventions but to date effective stigma-reduction interventions have not been tailored specifically for MOUD or for the rural primary care setting. Adapting MOUD-specific interventions that are feasible and acceptable for health care professionals practicing in rural areas is critical for improving access to buprenorphine in underserved rural communities.

This study includes developmental activities aimed at isolating the modifiable features of OUD-related stigma among rural health care professionals, adapting a brief stigma-reduction training intervention and finalizing the intervention with health care professional feedback, and implementing a two-arm randomized pilot trial among rural health care professionals to assess feasibility and acceptability of the intervention. We hypothesize that the brief stigma-reduction training intervention will be both feasible and acceptable in the rural primary care setting. Our specific aims are to:

Aim 1: Examine HCP knowledge and attitudes about OUD to understand their reluctance to prescribe MOUD and manage patients with OUD.

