## Outcome Measures:

| Type    | Name            | Time Frame | Brief Description                                                                                                                                                                                                                                                                                                                                                                                                                                                                                                                                                                                                                                                                      |
|---------|-----------------|------------|----------------------------------------------------------------------------------------------------------------------------------------------------------------------------------------------------------------------------------------------------------------------------------------------------------------------------------------------------------------------------------------------------------------------------------------------------------------------------------------------------------------------------------------------------------------------------------------------------------------------------------------------------------------------------------------|
| Primary | Acceptability   | 3 months   | 
Acceptability is the perception that the intervention is agreeable, palatable, or satisfactory to health care professional participants. Acceptability will be assessed qualitatively and quantitatively.
 
We will administer to participants the Acceptability of Intervention Measure (AIM), which comprises 4 items containing responses on a 5-point Likert scale. We will also record participants' perceptions and feedback about the intervention modules. In in-depth interviews, we will explore the stakeholders' perceptions of the content of the intervention, the need for it in rural practice settings, its potential effectiveness, and ease of delivery
 |

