| Primary | Feasibility     | 3 months   | 
Feasibility refers to the ease in which a new intervention can be used within a specific setting. It will be measured using the 4-item FIM. We will also measure feasibility through interviews with health care professional participants to understand barriers and facilitators of implementing the intervention in the rural primary care setting.
                                                                                                                                                                                                                                                                                                                          |
|         | Appropriateness | 3 months   | 
Appropriateness refers to the perceived alignment of the intervention within a particular practice setting and will be measured by the 4-item Intervention Appropriateness Measure (IAM). We will also measure appropriateness in in-depth interviews with health care professionals, exploring the most salient features of the intervention and its fit with current training needs.
                                                                                                                                                                                                                                                                                          |
| Primary | Adoption        | 6 months   | 
Adoption refers to intentions or actions to adopt an EBI. We will measure adoption as whether a HCP initiates buprenorphine prescribing for the first time or increases their patient panel (yes/no) and as the total number of patients receiving buprenorphine for each HCP. This measure will also allow us to measure preliminary effect sizes related to buprenorphine prescribing which are critical for the
                                                                                                                                                                                                                                                              |

|           |                                            |          |                                                                                                                                                                   |

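### The only quantitative primary analysis compares arms, but acceptability, feasibility and appropriateness are ratings of the training itself and need an intervention-arm estimate against a pre-set benchmark

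*Combined protocol and SAP*

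**What the plan says.** Quantitative data analyses sets a general rule: "All primary analyses will compare arms by measures of feasibility". Analyses of primary outcomes then gives one model: "We will specify a Gaussian error distribution and identity link to compare the means of each feasibility outcome between the two arms". That paragraph opens with the label "Buprenorphine prescribing outcomes" and describes repeated measures at 3 and 6 months. Expected effect size and power rests on a difference-in-differences design with two arms and claims adequate power for a one-SD difference on every primary outcome (d = 1.01).

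The Outcome Measures table defines the outcomes:

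- **Acceptability** (primary, 3 months): "Acceptability is the perception that the intervention is agreeable, palatable, or satisfactory to health care professional participants". On who responds: "We will administer to participants the Acceptability of Intervention Measure (AIM"), with no restriction to one arm.
- **Feasibility** (primary, 3 months), by the FIM: "Feasibility refers to the ease in which a new intervention can be used within a specific setting".
- **Appropriateness** (type cell blank, 3 months), by the IAM: the perceived fit of the training with the practice setting.
- **Adoption** (primary, 6 months): starting or expanding buprenorphine prescribing, and patient numbers. It can be measured in both arms.

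The hypothesis in 4.1.a is: "We hypothesize that the brief stigma-reduction training intervention will be both feasible and acceptable in the rural primary care setting". Section 4.1.c lists one intervention. For the control arm, the documents give only its size (2 clinics, n = 133).

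**The concern.** A score on the AIM, FIM or IAM is an opinion about a particular intervention. A difference in mean score between arms is interpretable only if it is known what each arm was rating. The documents say this for the intervention arm and are silent for the control arm.

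The hypothesis is also a statement about one arm. A large arm difference is compatible with a poor rating of the training, and no arm difference is compatible with a good one. Initial Data Inspection says that analysis details follow for each hypothesis. Yet no intervention-arm estimate, interval or target score appears.

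Aim 3 is to assess feasibility and acceptability in the pilot, and 4.1.a describes the primary outcomes as feasibility. If no criterion is fixed in advance, whether the training was acceptable would be decided after the scores are known.

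**Working it through.** **1. The plan's own figure.** The documents give N = 400, 6 clinics split 4:2, two-sided alpha 0.05, power 80% and retention 90%. They give no ICC and no baseline correlation, so d = 1.01 can be neither confirmed nor refuted. For a post-intervention comparison with m participants per clinic:

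detectable d = (1.960 + 0.842) × √[(1/4 + 1/2) × (ICC + (1 − ICC)/m)]

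With m = 60 (360 retained) and ICC = 0.16, this is 2.802 × √(0.75 × 0.174) = 1.01. With a t reference on 4 df, the ICC needed is about 0.08. With a difference-in-differences variance factor 2(1 − r), r from 0 to 0.7, it is about 0.07 to 0.28 (normal) or 0.03 to 0.15 (t). The figure is not shown to be wrong, and this point does not depend on it. What matters is its scope: it claims an arm contrast for every primary outcome. A difference-in-differences also needs a baseline value, and a rating of training not yet received has none in either arm.

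**2. The readings of the primary model, side by side.**

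| Reading | Consequence for AIM, FIM, IAM |
|---|---|
| Model covers them; controls answer | The contrast sets ratings of the training against ratings of something unspecified |
| Model covers them; controls do not answer | 133/400 = 33% missing, above the 10% trigger in Missing data. Control opinions would be imputed under MAR with no observed control scores to identify an arm effect |
| Model covers prescribing only | No quantitative analysis is specified |

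None of these yields a test of the 4.1.a hypothesis.

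**3. Precision of an intervention-arm estimate.** From the documents: 4 clinics, and 267 × 0.90 ≈ 240 retained. The 90% is a 6-month figure, used here for a 3-month endpoint. Assumed: SD 0.8 on the 5-point scale, and the ICC values shown.

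SE = 0.8 × √[ICC/4 + (1 − ICC)/240]; half-width = t(0.975, 3 df) × SE = 3.182 × SE

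| ICC (assumed) | Term under the root | SE | 95% half-width (points) |
|---|---|---|---|
| 0.01 | 0.0025 + 0.0041 = 0.0066 | 0.065 | 0.21 |
| 0.05 | 0.0125 + 0.0040 = 0.0165 | 0.103 | 0.33 |
| 0.08 | 0.0200 + 0.0038 = 0.0238 | 0.123 | 0.39 |
| 0.16 | 0.0400 + 0.0035 = 0.0435 | 0.167 | 0.53 |

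Using all 267 changes little: at ICC 0.05 the half-width is 0.403 SD instead of 0.408 SD, because the number of clinics dominates.

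**The case against.** The strongest reply is that the plan may never have meant to apply the model to these scales. Its paragraph is labelled as prescribing, its repeated measures are at 3 and 6 months while the scales have a 3-month time frame only, and feasibility serves in 4.1.a as an umbrella term for primary outcomes that include adoption. This stands as a real ambiguity. It does not rescue the plan: the general rule covers all primary analyses, the power claim covers each primary outcome, and under the narrow reading the scales are left without a quantitative analysis.

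Three stronger readings are tempting and are not supported:

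- **That controls never receive the training.** The documents do not say so. Usual practice, other training and delayed access are all left open. What can be said is that the control condition is undescribed.
- **That the hypothesis cannot be answered.** Intervention-arm scores will exist, the three constructs are also explored by interview, the 10 follow-up interviews are all in the intervention arm, and the 4:2 allocation was chosen to gain more data on the training. The gap is in the specified analysis and criterion, not in the data. Ten purposively selected interviews do not, however, replace a pre-specified estimate.
- **That every primary outcome is affected.** Adoption can be compared between arms, and the blank type cell leaves the primary status of appropriateness unstated.

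It is also fair to say that the half-widths describe the precision of the remedy, not the size of an error.

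**Conclusion.** The point holds in this form: the only quantitative primary analysis specified is a between-arm comparison; for the AIM, FIM and IAM that comparison is either uninterpretable as written or, on the narrower reading, absent; and neither reading tests the stated hypothesis. Two of the three outcomes explicitly labelled primary are affected, plus appropriateness. The plan should be corrected before analysis, because following its stated rule literally gives a result without a defined meaning.

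This rests on the text as supplied, which describes no control-arm content and no control wording of the scales. An intervention-arm analysis is workable: about ±0.21 to ±0.53 points for an ICC of 0.01 to 0.16, given the assumed SD of 0.8 and 240 retained.

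**What to change.** 1. Replace the sentence in Quantitative data analyses with wording to this effect: *AIM, FIM and IAM scores at 3 months will be summarised in the intervention arm only, as a mean with a 95% confidence interval that allows for clustering by clinic (4 clinics, t on 3 df), and judged against a benchmark fixed before data lock. Between-arm comparisons will be made for adoption and the secondary outcomes.*
2. Have the sponsor choose and record the benchmark, stating whether it applies to the point estimate, the lower confidence limit or both.
3. Limit the statement in Expected effect size and power to adoption and the secondary outcomes, and make the same change in Analyses of primary outcomes.
4. In Missing data, exclude control-arm AIM, FIM and IAM values from the 10% trigger and from imputation.
5. State the type of the appropriateness outcome.
6. Report module and booster completion alongside the scores if those records exist. Section 4.1.c ties CE/CME credit to completing the full training, but describes no completion log and does not tie the booster to credit.

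The cost is mainly SAP wording, with no new data for items 1 to 5. The drawbacks are wider intervals with 3 df and a commitment to a benchmark.
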